### 2.2. Sample Size, Randomization, and Allocation

A sample of 96 participants (48 per group) is needed for an 80% probability to identify a difference between the treatment and control group. The power analysis for the sample size estimation was based on the means, standard deviations, and clinical cut-off for the primary outcomes (RTS, TSDS; Williams et al., 2022c, 2023b). Drawing on previous research, we hypothesized a standard mean difference of between 0.36 and 0.52, between the treatment and control group, which translates to a 10–20% decrease in the primary outcomes (i.e., RTS, TSDS) for individuals at the endpoint of treatment. Given these effect estimates, with an alpha of 0.05, an 80% power, and a 20% attrition, we estimated a sample size of approximately 96 (48 per group) will be needed. This randomized controlled trial will use an ANOVA and t-test (alpha error level = 5%, two-sided) for independent samples.

This sample size will require tailored recruitment efforts, community partnerships, and culturally safe retention strategies throughout the trial. Given differential attrition rates for racialized communities, the research team will spend additional time at intake discussing barriers to participation, issues with attendance, and address any participant concerns. Additionally, the research team will offer flexible session meeting times (e.g., evenings and weekends), and telephone check-ins as needed. The research team shall also compensate participants for both their completed sessions and batteries of measures.

In terms of blinding, the trial research team will be unaware of the group allocation. This includes the principal investigator and project coordinator who are overseeing the trial implementation, research assistants who will support recruitment and data collection, and the statistician conducting the analysis. See Figure 1 for the participant flow diagram of the trial.

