### 2.12. Statistical Analysis

Descriptive statistics, including means, standard deviations, and frequencies, will be calculated for continuous primary and secondary outcomes. Differences in primary and secondary outcomes, including TSDS, RTS, change in symptoms, and therapeutic experiences, will be examined using a two-way mixed ANOVA with two or three within-subject levels of time (pre-test, post-test, and follow-up) and two between-subject levels of condition (HRTP and control). When there is evidence of sphericity violation, we will use the Greenhouse–Geisser correction (Greenhouse & Geisser, 1959). It is predicted that participants’ TSDS and RTS scores will decrease significantly over the course of the treatment. It is also predicted that TSDS and RTS scores at follow-up will be the same or lower than at the end of the treatment.

Both the short-term and long-term efficacy of the HRTP will be examined during the treatment (week 0, 4, 8), at the end of the treatment (week 12), and 4 months after the treatment (week 28). Assessment will take place at four time points for the treatment group (HRTP therapy; weeks 0, 4, 8, 12, and 28; see Table 1 for participants’ assessment schedule) and only two time points for the control TAU group (T0 and T4; see Table 1 for participants’ assessment schedule). Analysis will compare standard mean differences (SMDs) between the time points for the treatment group (weeks 0, 12, and 28) and the control group (weeks 0 and 12). Analyses will entail intent to treat (ITT) and include participants with pre-treatment and the last time point available as long as they attended at least one treatment session. We examine significant levels for the analysis as well as effect sizes. A significance level of *p* < 0.05 will be used for all tests.

For each outcome of interest, we will identify any significant Condition × Time interactions. When no interaction is found, significant main effects will be reported. Partial eta-squared (η2) was used to measure effect sizes for the ANOVAs. When significant interactions are found, post hoc tests of simple main effects will be used to examine the differences, *p* values will be included for all post hoc tests, and 95% confidence intervals (CIs) will be used for all *p* values less than 0.05. Additionally, we will conduct comparisons of baseline data for completers and non-completers. Subgroup analysis will be based on age, gender, and levels of racial stress and trauma.

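### The article names two efficacy tests without saying which one decides superiority, and its prediction and main-effect fallback can be met when HRTP is no better than TAU

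*Protocol article*

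**What the plan says.** Section 2.2 sizes the trial on a standardised difference between the arms of 0.36 to 0.52 at the end of treatment, and says: "This randomized controlled trial will use an ANOVA and t-test (alpha error level = 5%, two-sided) for independent samples". It calls neither test primary and does not say whether the t-test is on week-12 scores or on change.

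Section 2.12 specifies a "two-way mixed ANOVA with two or three within-subject levels of time" and two conditions. It gives a sequence: "For each outcome of interest, we will identify any significant Condition × Time interactions". After that, "When no interaction is found, significant main effects will be reported", while simple-effect tests follow only a significant interaction. The 0.05 threshold applies to every test. The t-test is not mentioned again. The prediction is that "TSDS and RTS scores will decrease significantly over the course of the treatment", with no reference to TAU. SMDs are formed between time points in each arm.

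Section 1.4 does state a comparative hypothesis, that change under HRTP exceeds change under control, and section 2.1 calls the trial a superiority trial. Section 2.9 and Table 1 measure TAU at weeks 0 and 12 only.

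**The concern.** A superiority trial needs one contrast between the arms, per primary outcome, that settles the question. Here the sample-size and analysis sections name different procedures, and neither is tied to the hypothesis of section 1.4.

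Two consequences follow. First, the prediction in 2.12 and part of the main-effect fallback concern change over time, whichever arm it occurs in. Participants enter with clinically relevant symptoms and both arms receive 12 sessions of therapy, so improvement in both arms is plausible. A significant time effect could then be read as support for HRTP. Second, if the t-test and the interaction test different quantities, the verdict may depend on which is put forward after the data are seen.

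**Working it through.** **Does the stated sample size show which test was meant?** The plan's figure is 96 in total for 80% power, two-sided 5% and 20% attrition. A two-sided independent-samples t-test needs 60 per arm at SMD 0.52 (120, or 150 after dividing by 0.8) and 123 per arm at SMD 0.36 (246, or 308). So 96 does not follow from the t-test. Values at or near 96 appear only under unstated choices at SMD 0.52:

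- one-sided with no attrition: 94;
- baseline-adjusted comparison with correlation 0.6 and attrition by division: 96;
- between-arm factor of a three-occasion ANOVA with correlation 0.5 and attrition by multiplication: 96.

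The sample size therefore does not identify the deciding test.

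**Inputs.** n = 48 × 0.8 = 38.4, taken as 38 analysed per arm. SMD is 0.36 or 0.52, from section 2.2. The correlation r between baseline and week 12 is not in the document and is assumed to be 0.3 to 0.8. Scores are taken as normal with SD 1 at both times. Each setting was simulated 40,000 times with two-sided tests at 5%.

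**Between-arm tests.** With SMD d, the approximate noncentralities are:

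- raw week-12 t-test: d√(n/2) = 0.52 × √19 = 2.27 for any r;
- Condition × Time on weeks 0 and 12, identical to a t-test on change: d√(n/2)/√(2(1−r)), which is 1.92, 2.27, 2.93 and 3.58 at r = 0.3, 0.5, 0.7 and 0.8;
- week 12 adjusted for baseline: d√(n/2)/√(1−r²), which is 2.38, 2.62, 3.17 and 3.78.

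The first two statistics correlate at √((1−r)/2), which is 0.59, 0.50, 0.39 and 0.32, so they can disagree often.

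| r | Power at 0.52: raw t-test | Interaction | Baseline-adjusted | t-test and interaction disagree at 0.52 | No effect: either significant |
|---|---|---|---|---|---|
| 0.3 | 0.61 | 0.48 | 0.65 | 0.32 | 0.088 |
| 0.5 | 0.61 | 0.61 | 0.73 | 0.33 | 0.091 |
| 0.7 | 0.61 | 0.83 | 0.88 | 0.35 | 0.092 |
| 0.8 | 0.61 | 0.94 | 0.96 | 0.37 | 0.094 |

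At SMD 0.36 the disagreement is 0.26 to 0.49. If the t-test is on change, the interaction F equals t², and disagreement and extra error from this pair are zero.

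**The fallback.** Suppose both arms improve by c = 0.5 SD and HRTP has no advantage. The time effect has noncentrality c√(n/(1−r)). At r = 0.3 this is 0.5 × √(38/0.7) = 3.68, and at r = 0.5 it is 0.5 × √76 = 4.36. It is significant in 95% and 99% of trials, and in practically all at r = 0.7 and 0.8. The interaction is null in 95% of trials and is nearly independent of the time effect. A null interaction with a significant time effect therefore occurs in about 0.95 × 0.954 = 0.91 of trials at r = 0.3, rising to 0.95 (simulated: 0.907, 0.938, 0.950, 0.951). With a common improvement of 0.3 SD, it is 0.56 to 0.93.

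**The case against.** Section 2.12 does give an order: interaction first, then main effects or simple effects according to the result. Section 1.4 states a between-arm hypothesis about change, which the interaction matches. With TAU measured only at weeks 0 and 12, that interaction is a t-test on change. Section 2.12 also lists symptom change among the outcomes, so the t-test of section 2.2 may be the same test under another name. The analysis plan, not shown, may name the deciding model.

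Much of this stands, and it rules out some stronger readings. A reader might infer that everything is tested with no order or that no comparative hypothesis exists; sections 2.12 and 1.4 say otherwise. A reader might count the SMDs as further tests, but they are effect sizes. A reader might treat a paired test within HRTP as a planned efficacy test. No section specifies one, and the sentence on decreasing scores is a prediction. Nor does the article say that either of two significant results would count as success.

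What remains is narrower. The order in 2.12 leaves the t-test of 2.2 unplaced, its fallback reaches an effect that does not compare the arms, and its prediction is not the hypothesis of 1.4. The two sections already commit to different wording, so an analysis plan that chose one would still leave the article to be corrected.

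**Conclusion.** The point holds in this limited form: no section links one test to the superiority hypothesis, and the prediction and part of the fallback can be satisfied with no HRTP advantage. The second part needs no assumption about the t-test. With equal 0.5 SD improvement, a null interaction with a significant time effect occurs in about 91 to 95% of trials (38 per arm, r 0.3 to 0.8, normal data). The plan says such effects would be reported. It does not say that they would be claimed as superiority, but it does not exclude that either.

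The disagreement of about 32 to 37% at SMD 0.52 and the false-positive chance of about 9% are conditional. They require a t-test on raw week-12 scores, and the 9% also requires that either result be taken as success. Neither condition is stated, so these figures show what the ambiguity could cost and are not an established error rate of the plan.

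**What to change.** In sections 2.2 and 2.12, name the same deciding between-arm contrast for each primary outcome: the week-12 difference adjusted for the baseline score. If the ANOVA is kept, use the Condition × Time interaction on weeks 0 and 12 only, because the assessment schedule gives no TAU data after week 12. The adjusted comparison uses data already collected and has power 0.65 to 0.96 at SMD 0.52 under the assumptions above, at least as high as either alternative at each correlation.

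Label the independent-samples t-test a sensitivity analysis and say which score it uses. Reword the prediction so that RTS and TSDS fall more under HRTP than under TAU from week 0 to week 12. State that the time main effect, within-arm changes and within-arm SMDs are descriptive and are not evidence of superiority.

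This needs no new participants, visits or measures. The cost is the wording and the loss of a second route to claiming success. The choice should be fixed before outcome data are compared by arm.

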## 2. Methodology

### 2.1. Trial Design and Setting

A parallel-group, single-blinded, two-arm randomized controlled superiority trial compares the effectiveness of HRTP to TAU with a 1:1 allocation ratio. Quantitative and qualitative data will be used to examine the effect of HRTP on racial trauma, depression (primary outcomes), and functioning (secondary outcomes). The trial will take place in an urban city in the province of Ontario, Canada.

Conducting the study in Ottawa contributes to the generalizability of the findings due to the city’s demographic and cultural diversity. As Canada’s capital, Ottawa attracts individuals from across the country and around the globe, providing a considerable mix of racial, ethnic, and linguistic communities. Based on the 2021 Population Census, Black people represented the largest racialized group at 8.5%, while Arabs and South Asian people each represented 5.8% of the total population of the city (Statistics Canada, 2021). As of 2021, there are also some 46,500 Indigenous people living in the Ottawa area, making up 3.2% of the population (Statistics Canada, 2021). This diversity means that the study is more likely to capture a range of lived experiences, cultural contexts, immigration histories, and socioeconomic backgrounds, thereby strengthening the external validity of the findings. A broad and varied participant pool will help ensure results are applicable to other urban centres and potentially even to more rural or international settings that share similar multicultural characteristics.

This study will follow the ethical principles of the Canadian Code of Ethics for Psychologists (CPA, 2017) and the Ethical Conduct for Research Involving Humans (TCPS-2, 2014). Informed consent will be obtained from all participants. The pilot study has been approved by the Research Ethics Board (H-02-22-7613) of the University of Ottawa, ensuring the protection of participant privacy and confidentiality. Participants may withdraw from the study at any time without consequence.

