The *TAU therapists* will also partake in minimal onboarding activities including reviewing the trial protocol and an orientation at the control group’s treatment clinic, at the authors’ host institution. Onboarding for both HRTP and TAU therapists occurs before the said individuals see their first client. Nevertheless, training for both the intervention and control arms will not stop there. Once actively seeing clients, study therapists will be required to partake in weekly group supervision meetings. These meetings will last up to 90 min and be led by licenced clinical psychologists with general clinical experience (if a TAU supervision) or the HRTP (if an intervention supervision). Several supervision groups will run simultaneously to ensure group numbers remain low. That is, no more than 15 active therapists will be assigned to a single group supervision at a time. Moreover, while admission to supervision groups will be staggered (i.e., client and therapist onboarding-dependant), once placed, therapists will typically remain within their assigned group until they no longer wish to be part of the study (for case continuity and to more easily monitor therapists’ clinical goal progress).

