### 2.7. Treatment as Usual (Control)

Given the lack of validated alternative treatments for the healing of racial trauma (Williams et al., 2021), a TAU control group will be used. As such, participants will be referred to treatment at the authors’ host institution’s community mental health clinic after the completion of the intake assessment. The said clinic employs a variety of evidence-based therapeutic approaches, including CBT, emotionally focused therapy, existential therapy, interpersonal therapy, and psychodynamic therapy. Participants within the TAU group will receive 12 sessions of one of the said therapies (supervisor dependent).

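### The planned tests ignore clustering by therapist and supervision group, so p-values and intervals are too optimistic if clients who share them have correlated outcomes

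*Protocol article*

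**What the plan says.** Section 2.1 describes a "two-arm randomized controlled superiority trial compares the effectiveness of HRTP to TAU with a 1:1 allocation ratio". Section 2.2 sets the size: "A sample of 96 participants (48 per group) is needed for an 80% probability to identify a difference". It rests on these inputs: "we hypothesized a standard mean difference of between 0.36 and 0.52, between the treatment and control group", and "with an alpha of 0.05, an 80% power, and a 20% attrition". The same section names the test: "This randomized controlled trial will use an ANOVA and t-test (alpha error level = 5%, two-sided) for independent samples". Section 2.12 specifies a two-way mixed ANOVA with a within-subject time factor and "two between-subject levels of condition (HRTP and control"). Neither section mentions a therapist term, a supervision-group term, an ICC or a design effect.

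The way care is delivered is described elsewhere:

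- Section 2.4: each participant is assigned a treatment group and a therapist.
- Section 2.5: therapists come mainly from one clinic, where about 50 doctoral students see clients at any given time. HRTP and TAU therapists have separate onboarding, completed before each sees a first client.
- Section 2.5: weekly group supervision is specific to the arm, therapists typically stay in their group, and "no more than 15 active therapists will be assigned to a single group supervision at a time".
- Section 2.7: "Participants within the TAU group will receive 12 sessions of one of the said therapies (supervisor dependent"), with approaches ranging from CBT to psychodynamic therapy.

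**The concern.** Clients are randomised one by one, but treatment reaches them through therapists who work under arm-specific supervision. Clients who share a therapist, a supervisor or, in the control arm, a supervisor's choice of therapy may have correlated outcomes. When the providers differ between arms, their variation becomes part of the variance of the arm difference, and individual randomisation of clients does not remove it. A test that treats all clients as independent leaves that part out.

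The standard error is then too small, the true type I error exceeds 5%, intervals are too narrow, and power is lower than a calculation without clustering shows. A chance difference between the therapists or supervision groups of the two arms could be reported as an effect of HRTP.

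**Working it through.** **1. The plan's own figure.** For two independent means, two-sided alpha 0.05 and 80% power, n per arm = 2 × (1.960 + 0.842)² / SMD².

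| SMD | n per arm | After 20% attrition (÷ 0.8) | Total |
|---|---|---|---|
| 0.52 | 59 | 74 | 148 |
| 0.36 | 122 | 153 | 306 |

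The stated 96 is not reproduced, even with no clustering. With 48 per arm less 20% attrition (48 × 0.8 ≈ 38), t-test power is 61% at SMD 0.52 and 34% at SMD 0.36. The gap between 80% and 61% is a separate sample-size problem. It matters here only because it leaves no slack for a design effect.

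**2. Is there clustering?** Supervision groups nested in arm are explicit in Section 2.5. Shared therapists are inferred: 96 / 50 ≈ 1.9 clients per therapist if about 50 take part, and more if fewer do. If 50 were split evenly, 25 per arm with at most 15 per group would need at least 2 supervision groups per arm.

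**3. Formulas.** With m clients per cluster, the design effect is DE = 1 + (m − 1) × ICC. The correct standard error is √DE times the stated one. The actual type I error of the unadjusted test is approximately 2 × [1 − Φ(1.96 / √DE)]. Example: m = 4 and ICC 0.05 give DE = 1 + 3 × 0.05 = 1.15, √DE = 1.072, and 2 × [1 − Φ(1.828)] = 6.8%.

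**4. Therapist level** (m and ICC assumed; type I error from 40,000 simulated t-tests with about 38 per arm and no true effect; the formula agrees to within about 0.2 percentage points):

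| Clients per therapist | ICC 0.01 | ICC 0.05 | ICC 0.10 |
|---|---|---|---|
| 2 | 5.1% (DE 1.01) | 5.5% (1.05) | 6.2% (1.10) |
| 4 | 5.3% (1.03) | 6.8% (1.15) | 8.7% (1.30) |
| 6 | 5.5% (1.05) | 8.2% (1.25) | 11.1% (1.50) |

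**5. Supervision-group level** (number of groups and ICC assumed):

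| Groups per arm | ICC 0.01 | ICC 0.02 |
|---|---|---|
| 2 groups of 19 | 7.0% (DE 1.18) | 9.5% (1.36) |
| 3 groups of 13 | 6.5% (1.12) | 7.8% (1.24) |

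**6. Power at SMD 0.52**, t-test with an effective 38 / DE per arm: 61% at DE 1.00, 55% at DE 1.15 (38 / 1.15 ≈ 33) and 44% at DE 1.50 (38 / 1.50 ≈ 25).

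**7. What testing at supervision-group level costs.** With 2 groups per arm there are 2 degrees of freedom, and power at SMD 0.52 is about 21% to 23% for ICC 0.02 to 0.01. With 3 groups per arm (4 degrees of freedom) it is about 35% to 38%.

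**The case against.** Several points on the other side are fair.

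- **Therapist sharing and nesting are inferred.** The protocol gives no number of clients per therapist and does not bar a trainee from working in both arms. If therapists were crossed with arm, their effects would partly cancel. This stands, and the point is worded accordingly. It does not touch the supervision groups, which are arm-specific by the text.
- **The one figure given allows a small effect.** About 50 students for 96 clients permits roughly 2 clients each, where the inflation is slight. A reader might infer that a handful of trainees per arm makes a type I error near 11% likely. The document does not support that: 11% needs about 6 clients per therapist and ICC 0.10.
- **Section 1.2 might be read as predicting a therapist effect on outcomes**, since it calls the clinician the main source of therapeutic safety. That passage concerns cultural safety, not variation in symptom scores, and the HRTP onboarding aims at a common standard. It is no evidence for a particular ICC.
- **The phrase about independent samples may only distinguish the two-sample from the paired test, and random effects are often left to an analysis plan.** The first half is plausible. But Section 2.12 fixes a model whose sole between-subject factor is condition, so the protocol states an analysis without clustering rather than leaving the matter open.
- **A reader might attribute the whole loss of power below 80% to clustering.** It is not so: the drop to 61% is there without clustering.
- **A therapist random effect may often be estimated as zero** when each therapist has about 2 clients and the ICC is small. The result is then close to the unadjusted test, which does no harm.

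**Conclusion.** The concern holds in a limited form. Sections 2.2 and 2.12 fix tests that treat clients as independent, while Sections 2.4, 2.5 and 2.7 describe delivery that makes correlation within arm plausible. For any positive ICC with clusters nested in arm, the stated p-values and intervals are too optimistic.

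The direction follows from the design. The size does not, because m, the number of supervision groups and the ICC are all assumed. It ranges from negligible (few clients per therapist, small ICC) to material: 6.8% in a middle case at therapist level, and up to about 9.5% at supervision level with a group ICC of only 0.02. The loss of power due to clustering alone is about 6 percentage points in that middle case (61% to 55%). This should be corrected, but it does not invalidate the design.

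**What to change.** In Sections 2.2 and 2.12:

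1. Record coded therapist and supervision-group identifiers for every participant and carry them into the analysis data.
2. Analyse the week-12 contrast between arms with a linear mixed model that has a random therapist intercept (nested in arm if therapists work in one arm only) and Satterthwaite or Kenward-Roger degrees of freedom. State whether therapists may work in both arms.
3. Report the estimated ICC.
4. Restate the power of the fixed sample of 96 with design effect 1 + (m − 1) × ICC, giving the m and ICC assumed.
5. Report an analysis at supervision-group level as sensitivity only. With 2 or 3 groups per arm it has too few degrees of freedom to carry the main conclusion.

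The cost is two extra variables and changed analysis wording, with no change to treatment, eligibility or visits. Intervals will be somewhat wider and the stated power less favourable. The random therapist intercept does not fully absorb variation between supervision groups, so that limitation should be stated when the results are reported.
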